# A prospective randomised controlled trial of operative *versus* non-operative management of fractures of the humeral diaphysis: the HUmeral Shaft Fracture FIXation (HU-FIX) Study protocol

**DOI:** 10.1186/s13063-019-3576-0

**Published:** 2019-08-05

**Keywords:** Humerus, Humeral, Shaft, Diaphysis, Fracture, Randomised controlled trial, Operative, Fixation, Non-operative, Bracing, Trauma, Patient outcome

## Abstract

**Background:**

Humeral shaft fractures constitute around 1% of adult fractures in the UK, with an annual incidence of approximately 13 per 100,000 population. Historically, these injuries have been primarily managed non-operatively, with operative fixation reserved for specific indications. Although some recent retrospective studies have suggested there are potential benefits of operative fixation over humeral bracing, there is a deficiency in level 1 evidence to support operative management as the primary treatment for humeral shaft fractures.

**Methods/design:**

This single-centre prospective randomised controlled trial aims to recruit 70 adult patients with an isolated closed fracture of the humeral diaphysis into one of two treatment arms: operative (*n* = 35) or non-operative (*n* = 35). The operative arm will undergo open reduction and internal fixation (ORIF) of the fracture using a standard fixation technique (plate and screws). The non-operative arm will be fitted with a prefabricated humeral brace until fracture union. All patients will be followed up for 1 year post-intervention. The primary outcome measure will be the Disabilities of the Arm, Shoulder and Hand (DASH) score at 3 months post-intervention. Secondary outcome measures will include pain, treatment complications, return to work or sporting activities, shoulder and elbow range of motion, radiographic assessment, EuroQol (EQ-5D) Health Outcome score and 12-item Short Form (SF-12) Health Survey score. A health economic analysis will be performed to compare the cost implications of each treatment strategy.

**Discussion:**

This randomised controlled trial will provide level 1 evidence comparing a standard ORIF technique against functional bracing for isolated closed humeral shaft fractures. The investigators hope that the study results will assist surgeons in their decision-making when managing patients with these injuries.

**Trial registration:**

ClinicalTrials.gov, NCT03689335. Registered on 28 September 2018 (retrospectively).

**Electronic supplementary material:**

The online version of this article (10.1186/s13063-019-3576-0) contains supplementary material, which is available to authorized users.

## Background

Fractures of the humeral diaphysis (humeral shaft fractures) constitute 1.2% of adult fractures in the UK, with an overall incidence of 12.9 per 100,000 per year [1]. These injuries are more common in women and have a bimodal age distribution, with peaks of prevalence occurring in younger adults following high-energy trauma and older adults following low-energy trauma [1–3].

Humeral shaft fractures are routinely managed non-operatively, with the widespread use of a prefabricated humeral brace, as first described by Sarmiento et al*.* in 1977 [4]. The purported benefits of this technique (over conventional plaster immobilisation) include rapid and uninterrupted osteogenesis and early mobilisation of the shoulder and elbow, thus enhancing functional outcomes [4]. Subsequent studies comparing bracing with plaster immobilisation have demonstrated faster fracture union, reduced rates of varus mal-alignment and confirmed functional advantages in terms of shoulder and elbow mobility [5, 6].

Although functional bracing has resulted in low rates of humeral shaft fracture nonunion in some series [7–9], others have reported nonunion rates of 10% or more [10–13], with the highest rate reported as 33% [14]. When fracture union does occur, the reported time to union ranges from 7.5 to 11.5 weeks [7, 9], during which time almost all activities of daily living are restricted, and there is a risk of skin breakdown and secondary cellulitis that can necessitate brace removal [13]. Moreover, while malunion is considered to be tolerated well by patients, the acceptable thresholds are based upon an historic series of just 32 patients, who were examined by a single author [15]. A more recent series has suggested that malunion and consequent loss of shoulder range of motion can occur in up to 38% of patients treated with a brace [16].

The perceived limitations of humeral bracing have brought about a gradually increasing role for operative fixation [17]. Although intramedullary nailing is considered feasible, published case series [18], reviews [19, 20] and randomised controlled trials [21, 22] have consistently recommended open reduction and internal fixation (ORIF) as the strategy of choice when surgery is indicated.

The primary aim of this trial is to determine whether any functional difference exists, according to the Disabilities of the Arm, Shoulder and Hand (DASH) score at 3 months post-intervention, between operative (ORIF) and non-operative management (functional bracing) of humeral shaft fractures. The secondary aim of this trial is to determine whether any difference exists in other clinically important outcomes (including pain, treatment complications, return to work or sporting activities, shoulder and elbow range of motion, fracture union, patient-reported outcome measures and economic costs) between ORIF and functional bracing of humeral shaft fractures in the year following the intervention.

## Methods/design

The Humeral Shaft Fracture Fixation (HU-FIX) Study is a single-centre prospective randomised controlled trial that aims to assess whether there is any difference in outcome between patients with a humeral shaft fracture who are managed operatively (i.e. with surgical fixation) and those managed non-operatively. The study will adhere to the principles in the latest Consolidated Standards of Reporting Trials (CONSORT) Statement [23]. The study will be performed at a large tertiary referral centre. The study received a favourable opinion from the relevant research ethics committee on 19 July 2018 (South-East Scotland Research Ethics Committee 01 reference 18/SS/0073). The study is sponsored by National Health Service (NHS) Lothian Research and Development and was approved on 10 September 2018 (project number 2018/0223). The study was registered with the ClinicalTrials.gov database, which is operated by the US National Library of Medicine, on 28 September 2018 (ID NCT03689335). The study is funded and co-sponsored by the Scottish Orthopaedic Research Trust into Trauma (SORT-iT).

The trial will include all eligible patients presenting to the study centre with an isolated closed fracture of the humeral shaft. The planned flow of patients through the study is as shown in Fig. 1.

**Fig. 1 Fig1:**
[figure not shown]
CONSORT flow diagram (with PRO extension) for the HU-FIX study. HU-FIX Humeral Shaft Fracture Fixation

A fracture of the humeral shaft (diaphyseal segment) is defined as any humeral fracture in which the major fracture line does not extend to within one metaphyseal width (Müller box) of either the shoulder or elbow joint; this is consistent with the *Arbeitsgemeinschaft für Osteosynthesefragen* definition [24], and is illustrated in Fig. 2.

**Fig. 2 Fig2:**
[figure not shown]
*Arbeitsgemeinschaft für Osteosynthesefragen* definition of humeral shaft (diaphyseal segment, 12-), with Müller boxes delineating the proximal (11-) and distal (13-) segments

### Inclusion criteria

Fracture of the humeral shaftClosed injuryAge ≥ 16 yearsAble to provide informed consent in EnglishSurgery performed within 3 weeks of date of injury

### Exclusion criteria

Completely undisplaced fracturesInjuries considered to be an absolute indication for surgery (including severe associated neurovascular injury, open fractures and bilateral injuries)Patients with a periprosthetic or pathological fracturePatients with an additional spine or limb injury (including those with polytrauma), which may impact upon functional rehabilitationPatients medically unfit for surgeryVery frail patients, defined as those with a Clinical Frailty Score of ≥6/9 as described in the Canadian Study on Health and Aging [25]Pregnant women with predetermined treatmentPatients declining operative managementPatients unable to comply with post-operative data gathering, including completing questionnaires in EnglishNon-residents or those unable to return to the Unit for the 1-year follow-up periodPatients for whom the treating surgeon does not feel that inclusion in the trial is in their best interests, either due to fracture pattern or patient factors

### Enrolment and allocation

Potential HU-FIX study participants will be identified at the point of referral to the Orthopaedic Service, either directly (via the on-call team) or via the Trauma Triage Clinic system [26]. Patients satisfying the inclusion and exclusion criteria will be introduced to the study by the treating clinical team and provided with a patient information sheet to read before being asked to participate. Patients will be predominantly enrolled into the study either on the Orthopaedic Ward (if admitted) or at their first outpatient clinic appointment. A study investigator will review the study protocol in detail with the patient and address any of their questions. If the patient is willing to participate, a study investigator will complete the informed consent process.

Once informed consent has been obtained, patients will be enrolled into the study by an investigator and randomly allocated to either operative or non-operative management of their humeral shaft fracture.

### Randomisation

The study will use a parallel assignment model, with 1:1 allocation of patients into each treatment arm (operative or non-operative). Randomisation will be stratified by patient age (< 65 years old or ≥ 65 years old), to ensure there are approximately equal numbers of younger and older patients in each treatment arm. Using block randomisation with a mixed block size and a 1:1 ratio of operative to non-operative, a computer-generated randomisation schedule was produced by a senior statistician from the local clinical research facility using nQuery Advisor v7.0 software (Statsols, Cork, Ireland). A member of staff independent of the study used this schedule to produce a series of opaque sealed envelopes, each containing a sticker bearing the words ‘operative’ or ‘non-operative’. Once the randomisation envelope is opened, the sticker is placed onto the already-signed consent form to indicate the treatment group allocation.

### Interventions

All patients will be initially treated in the Emergency Department with closed reduction of their humeral shaft fracture, and application of a either a U-slab or above-elbow hanging plaster cast.

Patients allocated to *operative* management of their humeral shaft fracture will undergo surgical fixation, using a standard technique of plating and screw fixation. The exact surgical approach and fixation technique utilised will be at the discretion of the treating surgeon. Similarly, post-operative immobilisation and range-of-motion restrictions will be at the discretion of the treating surgeon. This is determined by a number of factors including the injury and fracture pattern, bone quality, co-morbidities and patient compliance. The approach, fixation technique and range-of-motion restrictions will be recorded for all patients and presented as a sub-group analysis. Although the study sample will not be specifically powered on this basis (see Power calculation and statistical analysis, below), the investigators hope that a sub-group analysis will nonetheless allow any differences between the groups to be detected.

Patients allocated to *non-operative* management will be managed as per current standard practice for the study centre. This involves a period of immobilisation in a U-slab or hanging cast for up to 2 weeks, before fitting with a lightweight prefabricated humeral brace in the outpatient clinic. Two specific models of humeral brace are in routine use in this centre: the Clasby humeral brace (Beagle Orthopaedic, Blackburn, UK) and the ProCare over-the-shoulder humeral fracture brace (DJO Global, Vista, CA). The current standard of care in the study centre is to use the Clasby brace for proximal-third or mid-shaft fractures and the ProCare brace for distal-third or multifragmentary fractures. Brace selection for study participants will reflect these indications but will remain at the treating surgeon’s discretion. Patients will be permitted to start passive pendular shoulder exercises with full elbow, wrist and hand mobilisation as soon as the humeral brace has been applied. Post-injury physiotherapy will be arranged at the discretion of the treating surgeon, as occurs in everyday clinical practice.

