### Power calculation and statistical analysis

Prior to study commencement, a prospective power calculation was used to determine the number of patients required in each treatment group. The minimal clinically important difference in the DASH score is reported to be 10 points [32], and the assumed standard deviation is 12 points for both the operative and non-operative groups [33]. Thus, using a two-sided *t*-test with 5% significance, a total of 70 patients (35 in each group) are required to produce a 90% power to detect a meaningful difference (in terms of the DASH score at 3 months post-intervention) between the two groups, assuming a 10% loss to follow-up.

Data will be analysed on an intention-to-treat basis. Data analysis will be performed by a senior statistician, employed by the local clinical research facility and independent of the study team. The primary outcome measure (DASH score at 3 months post-intervention) will be compared between the two treatment arms, using a two-sided independent samples *t*-test or non-parametric equivalent (as indicated by the normality of the data). This method will also be used to compare the other continuous outcome measures between the two treatment arms (e.g. pain score, satisfaction scores, shoulder and elbow range of motion, EQ-5D score and SF-12 score). The pattern of change in continuous outcome measures over the study period will be presented graphically, broken down by treatment allocation. A linear regression model will be generated for each participant by plotting the DASH score from 6 weeks to 1 year post-intervention and the gradient of the regression line (i.e. the rate of change in the score) will be compared between treatment groups. Multivariate linear regression, including analysis of covariance (ANCOVA), will also be used to adjust for the potential effect of pre-injury DASH score, age and other prognostic factors affecting the DASH score. Binary outcomes (e.g. treatment complications, re-operation and nonunion or malunion) will be compared between the two treatment arms using a binomial test for the comparison of proportions. Two-tailed *p* values will be reported where possible, and statistical significance will be set at *p* = 0.05.

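### The planned sub-group analysis by surgical approach, fixation technique and motion restriction compares surgeon-chosen, post-randomisation groups, and the protocol caveats its power but not its confounding by indication

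*Protocol article*

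**What the plan says.** In the Interventions section of the protocol article, the paragraph on the operative arm leaves the approach, the fixation technique, and the post-operative immobilisation and motion restrictions to the treating surgeon. It then gives the basis of that judgement: "This is determined by a number of factors including the injury and fracture pattern, bone quality, co-morbidities and patient compliance". Grammatically this sentence follows the one on immobilisation and restrictions. That sentence opens by likening them to approach and technique, which are equally discretionary.

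The paragraph then commits to an analysis: "The approach, fixation technique and range-of-motion restrictions will be recorded for all patients and presented as a sub-group analysis". It concedes that the sample was not sized for this, and gives the purpose: "the investigators hope that a sub-group analysis will nonetheless allow any differences between the groups to be detected".

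The Randomisation section stratifies by age only (under 65, or 65 and over). No surgical factor enters the allocation. The Power calculation and statistical analysis section plans regression adjustment of the DASH score for pre-injury DASH, age and other prognostic factors, but does not connect it to these sub-groups.

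**The concern.** A sub-group analysis in a randomised trial keeps the protection of randomisation only when the sub-groups are defined by characteristics fixed before allocation. These three factors are decided afterwards, by a clinician looking at the patient and the fracture. The features that the protocol names as driving the decision are plausible predictors of DASH at 3 months in their own right. A difference between technique groups may therefore reflect which patients were given which technique.

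The only caveat in the text is about power. A reader would take from it that the analysis is sound but small, and that more patients would settle the matter. They would not. The trial is meant to help surgeons decide on management (Abstract, Discussion paragraph) and to inform future multi-centre work (main Discussion). A sub-group result announced in advance under an aim of detection could be cited as trial evidence on technique.

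**Working it through.** **1. The plan's own figure.** Inputs from the Power calculation and statistical analysis section: "The minimal clinically important difference in the DASH score is reported to be 10 points"; "the assumed standard deviation is 12 points for both the operative and non-operative groups"; two-sided test, 5% significance, 90% power, 10% loss.

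- n per arm = 2 × (1.96 + 1.2816)² × 12² / 10² = 2 × 10.51 × 1.44 = 30.3, so 31.
- Inflated for loss: 31 / 0.9 = 34.4, so 35 per arm and 70 in total.

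This matches the stated sample size. The t-distribution version gives 31.25, so 32 per arm, or 36 after inflation (72 in total), which is close enough to raise no question.

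**2. What each reading of the groups would compare.**

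- *Technique groups among operated patients.* Membership is chosen by the surgeon after allocation. Expected observed difference = effect of technique + difference due to case mix. Randomisation does nothing to make the second term zero.
- *Operative sub-groups against the brace arm.* The brace arm is the whole randomised arm and the operative sub-group is a selected part of its arm, so the two are no longer comparable by design. Approach and fixation technique are not defined for a braced patient, so no matching brace sub-group can be formed. The brace arm has a general mobilisation rule, but it is not described as a graded, surgeon-chosen level that could match the operative restrictions.

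**3. Why size does not help.** The case-mix term does not depend on n. Only the standard error does: SE = 12 × √(1/n₁ + 1/n₂). At 16/16 this is 4.24 points, and at 32/32 it is 3.00 points. Doubling the sample estimates the same confounded contrast more precisely.

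**4. Illustrative power within the operative arm.** Evaluable operated patients: 35 × 0.9 = 31.5, about 32. The splits are assumptions, because the document gives no expected frequency for any approach, technique or restriction. Power is from the noncentral t distribution with 30 degrees of freedom and noncentrality 10 / SE.

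| Split | SE | 10 / SE | Power for 10 points | Detectable at 80% | Detectable at 90% |
|---|---|---|---|---|---|
| 16/16 | 4.24 | 2.36 | 63% | 12.3 | 14.2 |
| 10/22 | 4.58 | 2.18 | 56% | 13.3 | 15.3 |
| 8/24 | 4.90 | 2.04 | 51% | 14.2 | 16.4 |
| 6/26 | 5.44 | 1.84 | 43% | 15.7 | 18.2 |

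With all 35 operated patients evaluable and split 17/18, power is 67%. These figures ignore confounding.

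**The case against.** The strongest reply has four parts.

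- **Position in the text.** The sentences sit in the operative-arm paragraph, so the groups most naturally mean technique groups among operated patients, and all patients means all operated patients. This stands. A reader might infer that the analysis cannot show anything because its factors have no brace-arm counterpart. The document does not support that: it never mentions a treatment-by-sub-group interaction, and a comparison among operated patients needs no counterpart. Such a comparison can show descriptive differences. It cannot attribute them to technique.
- **Power is already disclosed.** This also stands. The power figures above only put a scale on a limitation the authors state, and they rest on assumed splits. Likewise, the chance of at least one false positive, 1 − 0.95³ = 14%, applies only if exactly three independent tests at 5% are run. The document fixes no number of tests.
- **Details may be in a fuller document.** Choice of test, multiplicity and exploratory labelling can fairly be left to an analysis plan, and their absence is not the point here. The point is the stated aim of detecting differences with factors that no later plan can make randomised.
- **Confounders are acknowledged.** The protocol names the drivers of the surgeon's choice, plans covariate adjustment and stresses adjustment again in its Discussion. But none of this is tied to these sub-groups. About 32 operated patients leave little room to adjust for fracture pattern, bone quality, comorbidity and compliance together, and adjustment would not reliably remove confounding by indication.

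**Conclusion.** The point holds in a limited form. As written, the plan invites a non-randomised comparison, confounded by indication, under an aim of detecting differences, and the only limitation it admits is sample size. That conclusion rests on the text and not on the arithmetic: the choices are made after allocation by the surgeon and, at least for immobilisation and restrictions, on prognostic features that the protocol itself lists.

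Even without confounding, an assumed two-way split of about 32 operated patients gives 63% power at best for the protocol's 10-point difference, and 51% at 8/24.

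A reader might go further and conclude that the trial's main result or its sample size is compromised. The document gives no ground for that. The randomised intention-to-treat comparison of DASH at 3 months does not use these factors, and the total of 70 reproduces. The consequence is confined to what can be said about approach, technique and restrictions.

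**What to change.** Reword the two sentences at the end of the operative-arm paragraph in Interventions so that they say the following:

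- approach, fixation technique and motion restrictions are recorded for patients in the operative arm;
- they are reported as counts, with DASH summaries for each category and no hypothesis tests;
- these choices were made by the surgeon and were not randomised, so differences between the categories are not to be read as effects of technique.

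Delete the hope that differences will be detected.

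All planned data collection is kept, and no clinical choice, outcome or sample size changes. The cost is the loss of an inferential comparison of techniques, which this design could not have attributed to technique in any case.

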### Outcome assessment

All follow-up assessments will take place during outpatient clinic visits at 2 weeks, 6 weeks, 3 months, 6 months and 1 year. At each clinic visit, a physical examination will be performed, complications noted and the need for any further surgery recorded. Patients will be given time to complete a self-reported questionnaire, which will generate clinical outcome scores. The 1-year follow-up will enable study investigators to assess whether any differences between the operative and non-operative groups (if any) are sustained for 1 year post-intervention and to detect any important complications that may occur within the first year (e.g. nonunion).

The Standard Protocol Items: Recommendations for Interventional Trials (SPIRIT) [27] checklist is given in Additional file 1. The SPIRIT schedule of enrolment, interventions and assessments is shown in Fig. 3.

